## Sample size and power calculation

Test sample and statistical power is calculated by nQuery Advisor 5.0 software. The primary outcome is a change in verbal memory measured with RAVLT from baseline to week 12 between CR and standard treatment groups. A recent study demonstrated that the average California Verbal Learning Test (CVLT; a verbal learning test equivalent to the RAVLT) total recall score for patients with remitted bipolar disorder is 52.0 whilst healthy controls matched on age was 60.7 (out of maximum 75) [51]. Based on this, we would expect a clinically relevant difference in the change between groups to be at least 4 points in RAVLT total recall. Assuming an average RAVLT total recall score of 56 subsequent to CR and 52 (i.e. difference in the change of 4 points) subsequent to standard treatment and a standard deviation of 4 points for both groups, a sample size of N=40 patients (N=20 per group) will achieve a statistical power of 86% to demonstrate a clinically relevant verbal memory improvement with CR versus standard treatment.

**Statistical analyses of primary, secondary and tertiary outcomes**

For investigation of the effects of CR versus standard treatment from baseline to week 12 (primary outcome assessment time) we will use repeated measures analysis of covariance (ANCOVA) with adjustment for stratification variables, and with and without adjustment for mood changes from baseline to week 12. For investigation of long-term effects of CR versus standard treatment in week 26, we will implement a linear mixed effects model with random intercept for each participant, structured as a two-level model specifying a correlation of samples within participants, with adjustment for stratification variables, and with and without adjustments for mood changes. Significant interactions will be analysed further with simple main effect analyses. All statistical analyses of behavioural data, mood ratings and questionnaires will be performed using the Statistical Package for Social Sciences (SPSS).

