## Randomisation

Pharma Consulting Group [29] performed the randomisation of the patients with stratification for age (<35 years) and years of education (<15 years).

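### The primary repeated measures ANCOVA is in effect a change-score test that omits baseline RAVLT as a covariate: valid, but less precise than baseline-adjusted ANCOVA unless the baseline to week-12 correlation is very high

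*Protocol*

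**What the plan says.** The Protocol's section on statistical analyses of primary, secondary and tertiary outcomes fixes the model for the primary time point: "we will use repeated measures analysis of covariance (ANCOVA) with adjustment for stratification variables". The model is to be run in two versions, one of which also takes the change in mood over the same period as a covariate. The section adds: "Significant interactions will be analysed further with simple main effect analyses". The Randomisation section gives the stratifiers as age (cut at 35 years) and years of education (cut at 15 years). Baseline RAVLT is neither a stratifier nor a named covariate.

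The sample size section defines the endpoint in matching terms: "The primary outcome is a change in verbal memory measured with RAVLT from baseline to week 12 between CR and standard treatment groups". Its power inputs are a 4-point difference in change (means of 56 and 52), "a standard deviation of 4 points for both groups", and the claim that "a sample size of N=40 patients (N=20 per group) will achieve a statistical power of 86" per cent. It does not say whether the SD of 4 belongs to the score or to the change.

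**The concern.** The name ANCOVA suggests adjustment for the baseline value of the outcome. Here the covariates are age, education and, in one version, mood change. With two visits the model is a repeated measures model only if baseline RAVLT is one of the two outcome values, so the treatment test is group-by-time. That is a change-score comparison. It fixes the weight on baseline at 1, whereas a regression estimates that weight from the data.

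Two things are at stake in a trial planned on 40 completers. One is precision that the trial could have from a measurement it already takes. The other is sensitivity of the observed estimate to a chance baseline difference between arms, because subtracting the whole baseline over-corrects when r is below 1.

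**Working it through.** **Inputs from the protocol.** 20 per group; difference 4; SD 4; stated power 86%.

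**Assumptions.** Two-sided alpha 0.05 (neither alpha nor sidedness is stated); equal variance s² at both visits; correlation r between baseline and week 12, not given and so shown over a range. Strictly, r is the correlation after adjustment for age and education.

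**1. The plan's own figure.** Two-sample t test, 38 df, noncentrality 4 / (4 × √(2/20)) = 4 / 1.265 = 3.16. Power is 86.9%, so the stated 86% reproduces.

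**2. What the planned model tests.** With two visits, and covariates allowed to act on change over time, the group-by-time F equals the squared t for group in a regression of change on group and the same covariates. A check on simulated data with two binary stratifiers gave 21.762 both ways, on 36 residual df.

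**3. Relative precision.**
- Change score: residual variance 2(1−r)s².
- Baseline-adjusted ANCOVA: residual variance (1−r²)s² = (1−r)(1+r)s².
- Ratio, ANCOVA to change score: (1+r)/2.

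Estimating the baseline slope costs a little. With N = 40, two arms and a normally distributed baseline, the ANCOVA variance is multiplied on average by 1 + 1/(N−4) = 37/36 = 1.028.

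| r | (1+r)/2 | with slope cost |
|---|---|---|
| 0.5 | 0.75 | 0.77 |
| 0.7 | 0.85 | 0.87 |
| 0.9 | 0.95 | 0.98 |
| 0.95 | 0.975 | 1.00 |

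Simulation with 20 per arm agrees with the last column. The two methods break even where (1+r)/2 × 37/36 = 1, that is r = 72/37 − 1 = 0.946.

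**4. Power at 20 per group, difference 4.** ANCOVA uses 37 df. Where two values appear, the second includes the slope cost.

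*If 4 is the SD of change*, the ANCOVA residual SD is 4√((1+r)/2):

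| r | change score | ANCOVA SD | ANCOVA power |
|---|---|---|---|
| 0.5 | 87% | 3.46 | 94% |
| 0.7 | 87% | 3.69 | 92% / 91% |
| 0.8 | 87% | 3.79 | 90% / 89% |

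*If 4 is the SD of the score*, the change SD is 4√(2(1−r)) and the ANCOVA SD is 4√(1−r²):

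| r | change SD | change power | ANCOVA SD | ANCOVA power |
|---|---|---|---|---|
| 0.3 | 4.73 | 74% | 3.82 | 90% / 89% |
| 0.5 | 4.00 | 87% | 3.46 | 94% |
| 0.7 | 3.10 | 98% | 2.86 | 99% |

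**5. Chance baseline imbalance.** Given an observed baseline difference D, the expected change-score estimate moves by (1−r)D, in the direction opposite to D. If the score SD is 4, the standard error of D is 4 × √(2/20) = 1.26. A one-standard-error imbalance then moves the estimate by 0.3 × 1.26 = 0.4 point at r = 0.7, or 0.5 × 1.26 = 0.6 point at r = 0.5, against a 4-point target. Baseline adjustment removes this shift.

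**The case against.** The strongest reply is that nothing here is an error. The hypothesis, the endpoint definition, the power calculation and the model all target change from baseline to week 12, and under 1:1 randomisation a change-score test is valid. That stands. A reader might infer that the planned analysis is biased, or that the 86% is wrong. The documents support neither. Over randomisation the expected shift is zero and type I error is controlled; the (1−r)D shift holds only given the imbalance that happens to arise. The 86% reproduces.

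A reader might also infer that baseline adjustment always wins, or that a large imbalance should be expected. Neither follows. With 40 patients the advantage disappears at r of about 0.95. A 4-point baseline difference would be 4 / 1.26 = 3.2 standard errors if the score SD is 4, so it is not a fair illustration.

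The size of the gain rests on an r that the protocol does not supply, and on which reading of the SD applies. The SD is stated next to the post-treatment means; on that reading, at r = 0.7 the gain is only from 98% to 99%. This also stands.

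The last defence is that a full covariate list is commonly left to a statistical analysis plan, and that the protocol does not call its list exhaustive. This carries less weight. The protocol names the model and its covariates, and gives a second version with mood change; an analysis plan that followed it would inherit the loss.

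**Conclusion.** The point holds as one of efficiency. The primary model is a change-score comparison, and neither version adjusts for baseline RAVLT. Compared with baseline-adjusted ANCOVA, its variance is larger by a factor of about 2/(1+r) before the slope cost: 1.33 at r = 0.5 and 1.18 at r = 0.7. If the SD of 4 refers to change, that is worth about 7 percentage points of power at r = 0.5 and 4 to 5 at r = 0.7. If it refers to the score, it is worth about 7 points at r = 0.5 and 1 at r = 0.7. These figures assume two-sided alpha 0.05, equal variances at the two visits and the r shown. The algebra is certain; the size of the gain in this trial is not, because r is unknown. The change is worth making because the baseline score is already measured and the cost is small.

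**What to change.** Before unblinded analysis, restate the primary analysis as the between-arm difference in week-12 RAVLT total recall, with baseline RAVLT total recall as a continuous covariate together with the age and education stratifiers, reported with a 95% confidence interval. A mixed model for both visits with a common baseline mean across arms would serve equally well. Use the same form for RVP, TMT part B and FAST.

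The cost is one degree of freedom and a documented amendment of the model wording, since the protocol describes enrolment as ongoing. No new data are needed: the protocol already schedules cognitive and psychosocial assessment at baseline and week 12.

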**Outcome assessments**

The main study outcomes (cognitive and psychosocial function) and biomarkers of potential treatment effects (plasma BDNF, cortisol levels and neuroanatomical underpinnings) will be measured at baseline, after completion of treatment (week 12) and at follow-up (week 26). We also rate affective symptoms at these three time points and additionally at weeks 6 and 20 to uncover potential mood swings in the periods between outcome assessments

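### The week-26 random-intercept model, on its natural reading, assumes equal correlation between all visits; if correlation falls with time, the baseline-to-week-26 contrast can have too small a standard error (actual error 5% to about 10%)

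*Protocol*

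**What the plan says.** Protocol, Outcome assessments: the cognitive and psychosocial outcomes "will be measured at baseline, after completion of treatment (week 12) and at follow-up (week 26"), which makes three visits, 12 and 14 weeks apart. The additional visits serve mood ratings only: "We also rate affective symptoms at these three time points and additionally at weeks 6 and 20".

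Protocol, Statistical analyses of primary, secondary and tertiary outcomes: the week-12 comparison has its own covariance-adjusted analysis. For the later time point ("For investigation of long-term effects of CR versus standard treatment in week 26") the plan names a "linear mixed effects model with random intercept for each participant, structured as a two-level model specifying a correlation of samples within participants". It names no random slope, no residual covariance structure and no robust standard error. It does not write out which contrast represents the week-26 effect, but adds: "Significant interactions will be analysed further with simple main effect analyses".

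The protocol states no between-visit correlations and no significance level. Its only numerical design statement concerns week 12: a "difference in the change between groups to be at least 4 points in RAVLT total recall", with "a standard deviation of 4 points for both groups", for which "a sample size of N=40 patients (N=20 per group) will achieve a statistical power of 86" per cent.

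**The concern.** A two-level model with a random intercept and independent residuals implies compound symmetry: the same variance at each visit and the same correlation for weeks 0-12, 12-26 and 0-26. With three visits, the fitted common correlation is in effect the average of the three pairwise correlations.

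A natural measure of lasting benefit is the between-arm difference in change from baseline to week 26, because the primary outcome is also framed as a change. That change spans the longest interval. If scores 26 weeks apart correlate less than scores 12 or 14 weeks apart, the averaged correlation is too high for this contrast and its variance is understated. The p-value of a direct test, the confidence interval and any within-arm change from baseline to week 26 taken from the model would then all look more precise than they are. The statistical section covers primary, secondary and tertiary outcomes, so the restriction would apply to the verbal memory, attention, executive function and psychosocial measures alike.

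**Working it through.** **Inputs.** From the protocol: 20 patients per arm, visits at weeks 0, 12 and 26, random intercept per participant. Assumed, because the protocol does not give them: two-sided 5% level, complete data, equal variances over visits, and a range of between-visit correlations.

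**The plan's own figure.** With a difference of 4, SD 4 and 20 per arm, the noncentrality is (4/4) x sqrt(20/2) = 3.16. A two-sided 5% t-test with 38 degrees of freedom then has power 86.9%, in agreement with the stated 86%. This concerns week 12 only; the protocol gives no error rate or power for the week-26 model.

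**Formula.** Let s2 be the common variance and r(0,26) the correlation between baseline and week 26.
- True variance of one patient's change: 2 x s2 x (1 - r(0,26)).
- Variance used by the random-intercept model: 2 x s2 x (1 - mean of the three correlations).
- Ratio R = (1 - r(0,26)) / (1 - mean r).
- Model SE / true SE = 1/sqrt(R).
- Actual two-sided error, large-sample = 2 x (1 - Phi(1.96/sqrt(R))).

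**Worked case.** Correlation decays with time from 0.80 at 12 weeks:
- 0.80^(14/12) = 0.771 and 0.80^(26/12) = 0.617.
- Mean r = (0.800 + 0.771 + 0.617)/3 = 0.729.
- R = 0.383/0.271 = 1.41 and sqrt(R) = 1.19.
- The model SE is 0.84 of the true SE, about 16% too small.
- The effective critical value is 1.96/1.19 = 1.65, so the actual error is about 10% and a nominal 95% interval covers about 90%.

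**Range.** Correlations are in the order 0-12 / 12-26 / 0-26. The simulated columns use 20 per arm, 40,000 trials and no effect at any visit, with the split-plot tests to which the random-intercept model reduces when data are complete.

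| Correlations | R | Model SE / true SE | 0-26 contrast, formula | 0-26 contrast, simulated | Overall group-by-time test | Group difference at week 26 | 0-26 contrast, unstructured |
|---|---|---|---|---|---|---|---|
| 0.70/0.70/0.75 | 0.88 | 1.07 | 3.7% | not run | not run | not run | not run |
| 0.70/0.70/0.70 | 1.00 | 1.00 | 5.0% | 4.9% | 5.0% | 5.0% | 4.9% |
| 0.70/0.70/0.65 | 1.11 | 0.95 | 6.2% | not run | not run | not run | not run |
| 0.70/0.70/0.60 | 1.20 | 0.91 | 7.4% | 7.3% | 5.0% | 5.0% | 4.9% |
| 0.80/0.80/0.70 | 1.29 | 0.88 | 8.4% | 8.4% | 5.3% | 5.1% | 5.1% |
| 0.80/0.77/0.62 | 1.41 | 0.84 | 9.9% | 9.8% | 5.6% | 5.0% | 4.9% |
| 0.90/0.88/0.80 | 1.46 | 0.83 | 10.5% | 10.4% | 5.9% | 4.9% | 5.0% |

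The within-arm change from baseline to week 26, if taken from the same model, is inflated to a similar degree: 10.0% and 10.2% in the last two patterns.

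**The route through the interaction.** If the 0-26 contrast counts only when the overall interaction is also significant, the joint rejection rate under no effect at any visit is 2.5% with equal correlations, 4.4% for 0.80/0.80/0.70, 5.1% for decay from 0.80 and 5.5% for decay from 0.90.

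**The case against.** The strongest reply has four parts.

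1. **The wording is open.** The clause on within-participant correlation could describe a structure specified in addition to the random intercept, and the SAP, which was not available, may fix it. This stands as a caution. The more natural reading, however, is that the clause describes the correlation a random intercept induces, and no other structure is named. If one is meant, the sentence does not say which.

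2. **The described route is protected.** Follow-up analyses come after a significant interaction, and both that test and the group difference at week 26 hold close to 5%. This stands for p-values when there is no effect at any visit. It does not protect the confidence interval of the 0-26 contrast, which is too narrow whether or not the interaction is significant. It also fails if a real week-12 effect has vanished by week 26: the interaction then tends to be significant, and the contrast, if tested, returns to roughly 6-11% under decaying correlations.

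3. **Decay is assumed.** The protocol's background describes the targeted deficits as trait-like and persistent. A stable trait plus independent test error gives exactly equal correlations, for which the model is correct. This stands: the documents cannot place the trial within the range.

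4. **Week 26 is not the primary time point.** The first hypothesis ends at week 12, the others name no week-26 effect, and the discussion calls the study exploratory. This also stands and limits the weight of the point.

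A reader might infer that the week-26 analysis as a whole rejects a true null at twice the nominal rate. The documents do not support that: about 10% needs strong decay, and it applies to one contrast tested directly.

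**Conclusion.** The point holds in conditional form. If the week-26 model is a random intercept with independent residuals and correlation falls with time, three things can look too precise: the baseline-to-week-26 group contrast, its confidence interval and any within-arm change over that interval. The actual error at a nominal two-sided 5% is 5% under equal correlations, about 6-8% under mild decay and about 10% under strong decay; it is conservative if the 0-26 correlation is the highest. These figures assume complete data and equal variances, with correlations that were chosen, not taken from the protocol.

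It would go too far to say that the standard error is too small as planned, or that the trial's main conclusion is at risk. The primary week-12 comparison uses a separate analysis and is unaffected. The point is worth acting on because a readily available alternative holds 4.7-5.1% in every pattern simulated and needs no new data.

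**What to change.** In the Protocol's section on statistical analyses of primary, secondary and tertiary outcomes, replace the random intercept in the week-26 model with an unstructured covariance over baseline, week 12 and week 26 (three variances and three covariances), with Satterthwaite degrees of freedom. State that the week-26 effect of CR versus standard treatment is reported as a contrast with its 95% confidence interval from that model. In SPSS MIXED this is a REPEATED statement on visit with COVTYPE(UN).

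Fix in advance what happens if the model does not converge for an outcome. Either use a structure that lets correlation fall with time, such as first-order autoregressive or its heterogeneous version (the 12- and 14-week gaps are close enough to equal), or analyse the baseline-to-week-26 change directly. Heterogeneous compound symmetry is not a suitable fallback: it frees the variances but keeps the equal correlations.

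Cost: a sentence or two in the plan and one line of syntax. Error degrees of freedom for the contrast drop from (3 - 1) x (40 - 2) = 76 to 40 - 2 = 38, and the week-26 intervals become slightly wider. If the SAP already sets an unstructured covariance, the protocol sentence only needs to be brought into line with it.

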## Ethical considerations

The study is approved by The Regional Committee on Biomedical Research Ethics (protocol number H-1-2010-039), The Danish Data Protection Agency (protocol number 2010-41-4710) and ClinicalTrials.gov (identifier NCT01457235).

## Current trial status

Patient enrolment started in September 2011 and is ongoing until minimum 40 patients have completed assessment at week 12 (primary outcome assessment time).

**Discussion**

The present trial is the first RCT to investigate the effects of CR on cognitive function in BD. Data from patients with schizophrenia and preliminary results from small exploratory studies in mixed groups of patients with affective disorders suggest beneficial effects [16-19] although a recent study of functional remediation in BD showed no significant effect on cognition [20]. The present trial therefore serves to meet the clinical need for more specific and thorough investigations of the effects of CR on patients’ cognitive function.

*Limitations*

CR in a group setting has been investigated in a few studies only [15;20] and it is unclear whether if group therapy is less appealing than individual therapy for patients with cognitive difficulties. It is, however, our experience from the pilot study and patient feedback from the present trial that patients benefit from group based training; it is often easier for patients to acknowledge and accept their own cognitive difficulties and to learn to cope with them when they are aware of other patient’s problems and improvements. Another limitation is that it is unclear how many training sessions are optimal for bipolar patients with cognitive dysfunction. In the uncontrolled study by Deckersbach et al [18], 14 individual sessions of CR were provided and results showed lower residual symptoms and increased occupational and overall psychosocial functioning in patients with BD. Moreover, improvements in executive functioning were associated with improved occupational functioning. Studies of patients with schizophrenia have typically included an average treatment length of 32.2 hours (range=4-130), provided over 16.7 weeks (range=2-104) with a therapy intensity of 2.2 sessions per week (range=0.6-5) [15].

We chose to provide 12+1 sessions based on the experience from our pilot study that this length is sufficient for improvement in most patients. However, if this first exploratory study finds an effect of CR on cognition, future studies are warranted to explore the optimal length of treatment and frequency of CR sessions. Finally, the choice of a good control group is often complicated in psychological intervention studies. We chose to compare CR as an add-on to standard treatment with standard treatment alone. With such a design we cannot be sure that a potential beneficial effect of the active intervention is specifically due to the CR program or an unspecific effect of solely taking part in group sessions. Colom et al [52] used an elegant, however, also time and resource consuming design by comparing group psychoeducation with unspecific group intervention in their seminal paper aiming to detect the specific effects of psychoeducation. It can be argued whether if the interaction between patients in the unspecific group intervention is comparable to part of the CR treatment. Using our design, the entire combined effect of CR and group sessions, including the interaction with other patients with similar problems in-group sessions, is investigated.

### Advantages

RAVLT was chosen as the primary outcome measure for the following reasons: a) remitted patients with BD show deficits on this test [53;54]; b) it is a standardised, internationally accepted and valid test of verbal memory [55]; c) there is a high correlation between verbal memory and psychosocial function [56], which makes it clinically relevant; and d) other RCTs have found significant effects of CR on verbal memory in patients with schizophrenia [57;58;59]. However, there is also consistent evidence for trait-related deficits in sustained attention in BD and negative effects of this on psychosocial function [56]. In addition, CR has also been shown to improve attention in schizophrenia [57;59] and unipolar disorder [17], and both verbal memory and sustained attention are addressed in our CR programme. Therefore, the priority of verbal memory over sustained attention as the primary outcome may be somewhat arbitrary.

The study has a naturalistic approach with few exclusion criteria. Patients should suffer from BD, should be in complete or partial remission and should self-report cognitive difficulties. To make treatment with CR meaningful, patients with current substance or alcohol abuse or significant suicide risk are excluded but standard psychopharmacological treatment was allowed. Consequently, if CR is found to produce beneficial effects, the intervention can be implemented to treat all bipolar patients in complete or partial remission with subjective complaints of cognitive difficulties. We expect a high patient acceptance and adherence as the CR program is easy to follow, not too time consuming and due to the supportive positive effects from group setting in itself. From a feasibility perspective, the intervention is relatively inexpensive as two therapists in our affective disorder clinic deliver the group sessions. Although the CR intervention is standardised according to a manual and the computer training software [26;27] it is likely that treatment with CR is best offered in specialised affective disorder clinics with expertise within pharmacological and psychological treatment of bipolar disorder.

